### Data management

Research assistants enter questionnaire and clinical data into pre-programmed fields that minimize data entry errors, via REDCap management software. For ready access and analyses, data are stored in separate but linked databases, which contain a unique ID for each dyad within each record so that data can be easily linked across databases.

### Statistical plan

Our initial data analyses will include: 1) determining the distributions of outcome measures and assessing whether data transformations are needed, 2) insuring that the underlying assumptions of statistical analyses are satisfied, 3) identifying potential co-linearity problems, 4) identifying potential outliers that require further investigation, 5) confirmatory psychometrics for established psychosocial and developmental measures. For categorical variables, we will check for sparse cells and regroup categories if necessary. In building multivariable models, we will check linearity assumptions for continuous predictors and consider higher-order terms as appropriate. For missing data, sensitivity analysis will be performed to evaluate the impact of missing data on results, with consideration for implementing multiple imputation of missing values. We will apply Bonferroni correction when appropriate to adjust for multiple comparisons. Analyses will be carried out using R (including OpenMX SEM, and lme4 mixed modeling packages) and SAS.

Methods to summarize the complexity of 16S rRNA data continue to evolve. Individual Operational Taxonomic Unit (OTU) abundance, richness, alpha (within sample) and beta (between sample) diversity, dysbiosis scores, phylogeny-based or phylogeny-independent measures, and principal components are all used in microbiome analyses. To characterize the trajectory of gut microbiome acquisition, we will first calculate the relative abundances of individual taxa (e.g. *Bifidobacterium or Lactobacillus)* or the ratio of abundance of two taxa (e.g. *Lactobacillus*, *Proteobacteria*), as well as estimation of the alpha diversity with a measure such as the Shannon Diversity Index. Subsequent exploratory analysis will use principal components analysis and Unifrac distances as alternatives means for characterizing gut microbiome. The Shannon Index ranges from 0 to ln(x) where x is the number of taxa measured, but can be standardized to range from 0 to 1; the abundance of individual taxa can be a proportion or captured as a count variable (with log number of reads as offset) with the possibility of excessive frequency of zero counts; finally the ratio of the abundance of two taxa may be skewed, but can be log-transformed to range from minus to positive infinity. Thus in all cases the gut microbiome for a given infant at each point in time can be measured using continuous or count-based statistics and analyses which will be adjusted accordingly to accommodate log transformation, Poisson or zero-inflated Poisson processes, and overdispersion.

To best capture the richness of the data, analyses considering maternal prenatal stress will be carried out in a structural equation modeling (SEM) framework reducing measurement error for the latent construct of maternal prenatal stress. Based on exploratory examination of the measures we may consider a single latent prenatal stress variable, or possibly two (e.g. chronic/life course stress and acute anxiety/perceived stress). We will then estimate the association between the latent variable(s) and outcomes. Postnatal maternal stress measures will also be combined in a similar manner to capture overall stress burden across infant developmental periods. PNI function will be evaluated as the absolute levels of each cytokine and as the ratios of pro- to anti-inflammatory factors (e.g.*,* IL1/IL10), and may be log-transformed if indicated. Diurnal cortisol from the three samples will be estimated as the area under the curve (AUC). The NNNS total score will be incorporated into our analysis framework as our primary measure of newborn neurobehavior function. The Bayley III standardized scores for the mental, motor and behavioral instruments will be considered independently to separately characterize neurocognitive and socio-emotional development. Repeated administrations of the Bayley-III also allow for the analysis of trajectories of growth over time from 3- to 18-months of age.

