At the end of each visit, the research team reviews the stool and saliva sample collection procedures, and provides the mother with the sample collection supplies for that visit. This ensures that samples are collected correctly. During a day selected by the mother for sample collection, texts are sent to the mother 5-min before each of the scheduled saliva collections (at wakening; 30 min after awakening and at 8:00 pm) to remind her to collect the saliva samples from herself and her infant, and the stool sample from the infant’s diaper. The research staff then schedule a time with the mother to pick up the samples. This sample retrieval visit also allows the research staff to collect any final assessments or questionnaires that were not collected during the main visit.

Data collection, including what samples are collected at each time over the course of the 18-month protocol, is presented in Table 1. All infant stool samples are obtained by the mother using four Catch All swabs. The mother uses each swab to collect a small amount of stool and then places the sample back into pre-labeled hard plastic case. The samples are stored in the home freezer until collection by the study team, ideally within 72 h. Research staff transfer the samples into labeled Mobio tubes at the home or transport them to the research laboratory where the specimens are transferred into labeled Mobio tubes and stored in a − 80 freezer. At the time of analyses, samples are defrosted, and the DNA extracted using the MoBio isolation Kit according to the manufacturer’s protocol. DNA yields are quantified with the ThemoFisher Broad Range Quant-It kit. After extraction, the V3-V4 region of the 16S rRNA gene is sequenced according to previously published and standard HiSeq protocols. To minimize batch effects, sequencing is run with longitudinal maternal and infant samples on the same HiSeq plate, and randomized by collection site and maternal pregnancy outcome, e.g. preterm birth yes/no).

**Table 1 Tab1:** Biological and Questionnaire Data Collected at Each Time Point

Measure	Time Point	Group	Type of Assay/Analysis
Stool	1-week, 3-, 6-, 12-, & 18 month	Infant	Gut microbiome 16 rRNA gene sequencing
Blood	1-week & 18 month	Infant	Plasma cytokines
Saliva	3-, 6-, 12-, & 18 month	Infant, Mother	Diurnal cortisol, collected 3 times (at wake, 30 min after awakening, and 8 pm) & Salivary oxytocin
Buccal	1-week, 3, 6-, 12- month	Infant	HLA genotypes & DNA methylation

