Questionnaires	1-week, 3-, 6-, 12-, & 18 month	Mother	Perceived stress, depression symptoms, anxiety
Infant Feeding Survey	1-week, 3-, 6-, 12-, & 18 month	Mother	Maternal report of infant feeding sources
Infant Food Diary	3,6 and 12 month	Mother	Record of infant food consumption in 24 h period
Infant + Maternal Sleep & health	3-, 6-, 12-, & 18 month	Mother	Maternal report of infant and mother’s sleep patterns and illnesses, diagnoses, medications
Parental Bonding	6 months	Mother	Maternal report of their mother’s parenting style for first 16 years of life.
Stressful life events & Neighborhood safety	12-month	Mother	Measures on new life stressors and neighborhood and home safety
Sociodemographic	3, 12-month	Mother	Questionnaire on sociodemographic variables
Videotaped Observation	3-, 6-, 12-, & 18 month	Infant, Mother	Maternal-infant interaction style
NNNS	1-week	Infant	Infant neurodevelopment
Infant Cry	1-week	Infant	Cry quality for neural integrity
Bayley Scales	3-, 6-, 12-, & 18 month	Infant	Infant cognitive and social-emotional development
Child Growth Measures	1-week, 3-, 6-, 12-, & 18 month	Infant	Infant growth trajectory
Maternal Cognitive Assessment	Once at any visit	Mother	Measures memory, visual processing and information retrieval

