Preliminary testing will begin with a series of cross-sectional multivariable regression analyses testing the association between microbiome (e.g. Shannon Diversity Index) and PNI operationalized as the ratio of pro- to anti-inflammatory cytokines, or the cortisol AUC at each wave of follow-up. Next linear growth curve models with time invariant covariates and baseline microbiome predicting PNI trajectories will be fit to estimate the role of initial gut microbiome conditions on subsequent infant PNI trajectories. Finally fully longitudinal growth curve models including time-varying (e.g. microbiome measure trajectories) and time-invariant predictors will be estimated. Alternative mixed effects longitudinal models will be compared using Akaike Information Criterion (AIC) fit statistics. We will also test the association between PNI (now serving as a predictor variable) and infant development measured with the NNNS, and Bayley.

### Analysis for Aim 3

We will directly test the association between microbiome abundance or diversity, and trajectories in infant neurocognitive and socio-emotional development as measured using the Bayley. The modeling strategy will be similar to Aim 2 with initial exploratory and descriptive modeling followed by fitting a series of longitudinal growth curve models with time-varying and invariant covariates. Finally, we will include a series of candidate modifiers of the effect of microbiome on child development, operationalized as interaction terms. The candidate moderators include maternal post-natal stress, and maternal-infant interaction. These moderator models permit the estimation of possible heterogeneity of the association of microbiome and development.

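### Diurnal cortisol is summarised as an AUC over an interval that runs from waking to a fixed 8 pm, with no time standardisation or AUC type stated; taken as written, the measure moves with waking time

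*Protocol article*

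**What the plan says.** In the protocol article, Data collection schedules saliva "at wakening; 30 min after awakening and at 8:00 pm", and Table 1 repeats these three times for infant and mother at 3, 6, 12 and 18 months. The Statistical plan reduces them to one number: "Diurnal cortisol from the three samples will be estimated as the area under the curve (AUC". Analysis for Aim 2 then relates the microbiome to a cytokine ratio "or the cortisol AUC at each wave of follow-up" and goes on to growth curve models of psychoneuroimmunologic (PNI) function. The direction is later reversed: "We will also test the association between PNI (now serving as a predictor variable) and infant development".

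The article does not say whether the AUC is taken with respect to ground or to increase, whether it is divided by time, or whether waking time enters any model. Table 1 lists "Maternal report of infant and mother’s sleep patterns and illnesses, diagnoses, medications" at the same four visits, but nothing links these reports to the AUC.

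**The concern.** An area under a concentration curve has units of concentration multiplied by time. Here the first two samples follow waking and the third is tied to the clock, so the length of the interval differs between participants and can differ between visits. Two infants with the same three cortisol values get different AUCs if one wakes earlier.

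The measure matters for Aim 2. Cytokines are measured in blood only at 1 week and 18 months, whereas cortisol is measured at four visits. Of the two PNI measures that Analysis for Aim 2 names, cortisol AUC is therefore the only one with more than two time points. (Salivary oxytocin is also collected at four visits, but that section does not use it.) Variation in waking time adds noise to this measure. If waking time also shifts with infant age, feeding or stress, part of a cortisol trajectory or association would reflect interval length and not cortisol.

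**Working it through.** The article gives no AUC figure to reproduce.

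**Inputs.** From Data collection and Table 1: samples at 0 h (waking), 0.5 h and T, where T is the number of hours from waking to 8 pm. Waking times and cortisol values are assumptions, because the article gives neither.

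**Ground AUC by the trapezoid rule.** With values c0 (waking), c30 and c8:

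AUCg = 0.5(c0 + c30)/2 + (T − 0.5)(c30 + c8)/2

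**Example.** Assumed values 10, 14, 3 in arbitrary units, the same in both cases:
- Waking at 8 am, T = 12: 0.5 × 24/2 + 11.5 × 17/2 = 6 + 97.75 = 103.75.
- Waking at 5 am, T = 15: 6 + 14.5 × 17/2 = 6 + 123.25 = 129.25.
- Ratio: 129.25/103.75 = 1.246.
- Divided by T: 103.75/12 = 8.65 and 129.25/15 = 8.62.

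**Range.** Ratio of AUCg for the earlier to the later waker, over five assumed profiles (1, 1, 1; 10, 15, 2; 10, 10, 3; 10, 7, 1; 6, 6, 4):

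| Waking times compared | Difference | Ratio |
|---|---|---|
| 6 am v 7 am | 1 h | 1.07–1.08 |
| 6 am v 8 am | 2 h | 1.16–1.17 |
| 5 am v 8 am | 3 h | 1.24–1.25 |
| 6 am v 9 am | 3 h | 1.26–1.27 |
| 5 am v 9 am | 4 h | 1.35–1.36 |
| 6 am v 10 am | 4 h | 1.38–1.40 |

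The shape of the profile hardly matters, because AUCg is close to proportional to T. For constant cortisol it is exactly proportional. One hour is then 1/13 = 7.7% at a 7 am waking, and somewhat more on a shorter day (11/10 = 1.10 for 9 am against 10 am).

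**Noise.** For constant cortisol and a mean waking time of 7 am (T = 13), an assumed SD of waking time of 0.5, 1 or 1.5 h gives the AUC a coefficient of variation of 0.5/13 = 3.8%, 1/13 = 7.7% or 1.5/13 = 11.5% from interval length alone.

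**AUC with respect to increase.** AUCi = AUCg − c0 × T. For the values 10, 14, 3:
- T = 12: 103.75 − 120 = −16.25.
- T = 15: 129.25 − 150 = −20.75.

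The size changes by 20.75/16.25 = 1.28. A constant profile gives 0 at any T, so the size of this dependence varies with the profile.

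**After dividing by T.** For 6 am against 9 am, the ratio of AUCg/T lies between 0.99 and 1.00 over the five profiles.

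**Weight of the waking sample.** At T = 13 the shares in AUCg are 0.25/13 = 1.9% (waking), 6.5/13 = 50.0% (+30 min) and 6.25/13 = 48.1% (8 pm). Dividing by T leaves these shares as they are. In AUCi the weights are −12.75, +6.5 and +6.25, so there the waking sample has the largest weight in size.

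**The case against.** The strongest reply is that a journal article condenses the plan and that the formula for a derived variable belongs in the full protocol or analysis plan. A reader might infer from the text that the AUC is known to be unscaled. The article does not say that, and it may be scaled in a document not shown. This part of the reply stands: the point is that no scaling is stated. It does not dispose of the matter, because the article does fix a start that varies, an end that does not, and an area as the summary. Followed literally, these three together produce a measure that depends on interval length.

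A second reply is that other parts of the plan could deal with it. Confounders for all aims are to be considered with directed acyclic graphs, sleep patterns are reported at the saliva visits, and Aim 2 allows time-varying predictors. None of these excludes an adjustment for waking time, but none mentions one. A log transformation would not help, since it turns the factor T into an added log T.

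Third, bias needs waking time to be related to age, feeding, stress or the microbiome. The article gives no data on this. Without such a relation the effect is noise only.

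A reader might also infer that the waking sample is almost ignored. That holds for a ground AUC (about 2%) but is reversed for an AUC with respect to increase, and the article does not say which is meant. It is separate from interval length. A ground AUC is meant to summarise total output, so wanting a slope or an awakening rise is a preference for another quantity.

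**Conclusion.** The point holds as a weakness in a stated measure that should be corrected. It does not show that the final analysis will be wrong. Under an unscaled trapezoid ground AUC, identical cortisol values give results that differ by about 7–8% per hour of waking time around 7 am, about 25% over 3 hours and up to about 40% over 4 hours. The 25% should not be read as an upper bound or as an observed effect, since it comes from an assumed 3-hour contrast. An AUC with respect to increase would not avoid the dependence. The added noise needs only that waking times vary; bias rests on the further assumption that they vary with age, feeding or stress. All ratios hold cortisol values fixed and so show the effect of interval length alone.

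**What to change.** Define the cortisol measure as the ground AUC divided by the hours between the first and last sample, using actual collection times. This is a time-weighted mean concentration. Use it wherever cortisol enters Aim 2, as outcome and as predictor. The alternative is to keep the AUC, state its type, and include the interval length as a covariate in each of those models.

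The change takes one line in the definition of the derived variable. Its cost is that clock times of collection must be recorded for each sample. Reminder texts are sent 5 minutes before each scheduled collection, so planned times should exist. Where actual times were not kept for samples already collected, planned times could serve as an approximation, declared as such. A slope from waking to 8 pm and a 0–30 minute rise can be added if the investigators want the diurnal pattern as well. They are optional and not part of this correction.

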Preliminary testing will begin with a series of cross-sectional multivariable regression analyses testing the association between microbiome (e.g. Shannon Diversity Index) and PNI operationalized as the ratio of pro- to anti-inflammatory cytokines, or the cortisol AUC at each wave of follow-up. Next linear growth curve models with time invariant covariates and baseline microbiome predicting PNI trajectories will be fit to estimate the role of initial gut microbiome conditions on subsequent infant PNI trajectories. Finally fully longitudinal growth curve models including time-varying (e.g. microbiome measure trajectories) and time-invariant predictors will be estimated. Alternative mixed effects longitudinal models will be compared using Akaike Information Criterion (AIC) fit statistics. We will also test the association between PNI (now serving as a predictor variable) and infant development measured with the NNNS, and Bayley.

### Analysis for Aim 3

We will directly test the association between microbiome abundance or diversity, and trajectories in infant neurocognitive and socio-emotional development as measured using the Bayley. The modeling strategy will be similar to Aim 2 with initial exploratory and descriptive modeling followed by fitting a series of longitudinal growth curve models with time-varying and invariant covariates. Finally, we will include a series of candidate modifiers of the effect of microbiome on child development, operationalized as interaction terms. The candidate moderators include maternal post-natal stress, and maternal-infant interaction. These moderator models permit the estimation of possible heterogeneity of the association of microbiome and development.

### Power calculations

The study will enroll approximately 300 mother-infant dyads from the parent study for further follow-up. Because of the various complex relationships hypothesized in this project, power calculations were carried out using Monte Carlo simulations of hypothesized data generating processes permitting empirical estimation of coverage and power as a function of sample size and standardized effect sizes, *d:*
$$ \frac{\left({\mu}_1-{\mu}_0\right)}{\sigma } $$. Aim 1 concerns the association between prenatal stress (measured in the parent study) and infant microbiome at baseline for the follow-up study, thus the full sample will be available. Using multiple indicator variables for the latent construct of prenatal stress can reduce measurement error and improve power. For example we estimate 93% power to detect a correlation between prenatal stress and Shannon Index of diversity of *r = .22*, and 78% power to detect a correlation of *r = .18*. Aims 2 and 3 rely on analysis of repeated measures data at 1 week, 3-, 6-, 12-and 18-months; based on investigator experiences in longitudinal studies we anticipate at most 20% loss to follow-up resulting in N = 240 for longitudinal analyses. For example for Aim 3 we estimate 82% power to detect correlation in microbiome diversity and the rate of change (latent slope) in the Bayley of *r = 0.15*. Power is similar for other longitudinal hypotheses.

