Despite the burgeoning number of theoretical papers describing the microbiome and its potential role in infant neurodevelopment, there are only a handful of empirical studies that have tested the infant gut microbiome in association with prenatal stress and infant outcomes, and none that have examined these relationships in an African-American sample of infants. To address these knowledge gaps and assess the roles of stress, genetics, and the microbiome in neurodevelopment of African American infants, we have developed the Emory University African American Stress and Infant Gut Microbiome Cohort Study.

The objective of this report is to present the research design, data collection and laboratory methods of our the Emory University African American Maternal Stress and Infant Gut Microbiome Cohort Study, and to identify how this protocol will lead to the completion of the following Study Aims: to: 1) Characterize the relationship between maternal prenatal stress and infant gut microbiome at 1-week of age; 2) Evaluate the pathways between infant gut microbiome, PNI function, and infant neurocognitive and social-emotional development from 1-week to 18-months; and 3) Evaluate the associations among the infant gut microbiome, maternal caregiving and stress, and infant neurocognitive and social-emotional development from 1-week to 18-months.

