### Participant recruitment

Women who are completing prenatal visits associated with the parent study (at the second prenatal care visit occurring between 24 and 30 weeks) are provided information about the study by a member of the parent study staff. Participants who express interest in the infant follow-up study are encouraged to text the infant study coordinator at that time, and are provided the contact information. The infant study coordinator also are directly provided the list of names and contact information for all women who complete the second prenatal study visit and who consented to share this information. Continuing contact efforts consist of texts and phone calls, and women who express an interest in participating in the infant study are scheduled for enrollment approximately one week following their estimated date of delivery.

Women in the parent and infant studies move frequently and change phone numbers frequently. Efforts to reconnect include calling any listed contacts, and checks of White Pages. Ongoing efforts are made to enroll women in the study at any one of the study time points that they are contactable, unless or until participation is refused. Recruitment is ongoing and includes 185 study participants to date. Active refusals constitute 9%. Retention rates are approximately 80–85% throughout the infants’ first year.

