### Data collection

Maternal prenatal stress data are collected two times during pregnancy (at the first prenatal care visit occurring between 8 and 14 and at a later prenatal care visit occurring between 24 and 30 weeks). Prenatal stress measures include self-reported stressful life events, perceived stress, perceived discrimination, state anxiety and depressive symptoms, as well as hair cortisol collection. Medical record abstraction is conducted by trained research staff for evidence of pregnancy infections, complications and treatments, and laboratory outcomes. Post-delivery medical record abstraction is detailed for birth outcome (gestational age, birth weight, size-for-age), delivery type, and complications.

Postnatal study visits occur at five times (1-week, and 3-, 6-, 12-and 18-months) post-birth and consist of biological samples, questionnaire data, and infant assessments. Data collection is conducted in participants’ homes or at the university laboratory by experienced research staff, trained in all aspects of the protocol. To the greatest degree possible, all home visits except the 1-week visit are scheduled for ±2 weeks of the designated time; the 1-week visit are scheduled for ±2 days. For infants born premature, the initial 1-week visit (and other follow up visits) are scheduled according to the corrected gestational age.

Enrollment and consent occur at the first postpartum study visit in which the dyad participates. Mothers provided consent for their own and their infant’s participation. Following consent, infant neurodevelopmental assessments (*NICU Network Neurobehavioral Scale* [NNNS] at 1-week [41] or Bayley Scales at 3-,6-,12-, and 18-month visits [42]) and growth measures (height, weight, and head circumference) are administered by trained research staff while the mother fills out questionnaires concerning her current demographic status, her home environment, her recent stress, her infant’s diet, and her and her infant’s sleep and health. At the 3-, 6-, 12- and 18- month visits, mothers and infants are then videotaped during a 5 min structured and a 5 min unstructured mother child interaction. At the one week and 18-month visits, blood is collected from the infant via heel stick and finger stick respectively, for the purpose of assessing cytokine levels (PNI functioning). Swabs are then used to collect infant cheek cells for DNA analyses at the 3-month visit.

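### The Aim 1 power statement assumes a 1-week stool from the full sample, but dyads may first enrol at any later visit and no allowance is made for this

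*Protocol article*

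**What the plan says.** The study aims, at the end of the Background, set Aim 1 as: "Characterize the relationship between maternal prenatal stress and infant gut microbiome at 1-week of age". The outcome is therefore tied to one age.

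The Power calculations section opens with the target: "The study will enroll approximately 300 mother-infant dyads from the parent study for further follow-up". It then reasons that Aim 1 uses prenatal stress from the parent study and "infant microbiome at baseline for the follow-up study, thus the full sample will be available". Two results follow directly: "we estimate 93% power to detect a correlation between prenatal stress and Shannon Index of diversity of" r = 0.22, and "78% power to detect a correlation of" r = 0.18. An allowance of at most 20% loss, giving N = 240, appears next, but only for the longitudinal Aims 2 and 3.

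Entry to the cohort is described elsewhere. Participant recruitment states: "Ongoing efforts are made to enroll women in the study at any one of the study time points that they are contactable", until participation is refused. Data collection states: "Enrollment and consent occur at the first postpartum study visit in which the dyad participates". The same section gives the first visit a narrow window: "the 1-week visit are scheduled for ±2 days".

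**The concern.** The power section moves from the outcome being a baseline measure to everyone having it. That step is valid only if every dyad enters at 1 week. Under the stated rule, a dyad first reached at 3, 6, 12 or 18 months is enrolled and counted, but its 1-week sample can never be collected. The number of dyads available for Aim 1 is then smaller than the number enrolled, by an amount the article does not state.

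What is at stake is the precision of the first aim. The r = 0.18 scenario starts at 78%, so it has little room for loss. A second, smaller issue is who lacks the sample. Late entry follows from being hard to contact, and the recruitment section says that women in both studies often move and change phone numbers. That may be related to stress, which is the Aim 1 exposure, although the article does not say so.

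**Working it through.** **Inputs.** From Power calculations: about 300 dyads; 93% power at r = 0.22; 78% power at r = 0.18; a 20% loss allowance for Aims 2 and 3 only. Not given: alpha, sidedness, the number of stress indicators, their loadings, and the share of dyads without a 1-week stool. Two-sided 5% is assumed throughout (critical value 1.960).

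**Step 1. Can the stated figures be reproduced at N = 300?** For a correlation, Fisher's z gives power = Φ(atanh(r)·√(N − 3) − 1.960).

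- r = 0.22: atanh = 0.2237, √297 = 17.23, product 3.854. Φ(1.894) = 97.1%.
- r = 0.18: atanh = 0.1820, product 3.136. Φ(1.176) = 88.0%.

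The plain formula therefore does not return 93% and 78%; the stated values are lower. Two explanations fit:

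- *Smaller effective N.* Solving for N gives (3.436/0.2237)² + 3 ≈ 239 for the first figure and (2.732/0.1820)² + 3 ≈ 228 for the second. At N = 240 the plain formula gives 93.1% and 80.0%.
- *N = 300 with measurement error in stress.* The observed correlations needed are 0.197 and 0.157. Those are 0.894 and 0.873 of the nominal values, so the implied reliability is about 0.80 and 0.76. A simulation check, using a mean score of five indicators with loadings of 0.7 at N = 300, gave 93.4% and 81.3%. Three such indicators gave 90.8% and 77.0%.

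The article reports Monte Carlo simulation with a latent stress construct, so the second explanation is natural, but nothing in the text settles it.

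**Step 2. Effect of missing 1-week stools if the figures were simulated at N = 300.** The implied noncentrality is 1.960 + 1.476 = 3.436 for 93%, and 1.960 + 0.772 = 2.732 for 78%. Each is scaled by √((N − 3)/297). The missing share is an assumption, shown as a range.

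| Assumed share without 1-week stool | N | Power, r = 0.22 | Power, r = 0.18 |
|---|---|---|---|
| 0% (as stated) | 300 | 93% | 78% |
| 10% | 270 | Φ(3.258 − 1.960) = 90% | Φ(2.590 − 1.960) = 74% |
| 20% | 240 | Φ(3.069 − 1.960) = 87% | Φ(2.441 − 1.960) = 68% |
| 30% | 210 | Φ(2.868 − 1.960) = 82% | Φ(2.281 − 1.960) = 63% |

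**Step 3. The alternative.** If the simulation in effect used about 228 to 240 dyads with stress measured without error, the printed power would already survive roughly 20% without a stool. In that case the power stands, but the sentence giving its basis is wrong.

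**The case against.** The strongest reply is that no error in 93% or 78% has been shown. This stands. A reader might infer that Aim 1 power is certainly overstated. The article does not support that, because the simulation inputs are not given and the stated pair lies below the plain N = 300 values, close to those for about 228 to 240 dyads.

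The share of late entrants could also be small. Interested women are scheduled for enrolment about a week after the estimated delivery date, and later entry is the fallback for those who could not be reached. The target is at least 300 (Study design), drawn from a parent cohort of over 500, so 300 is not a ceiling. These points limit the size of the effect; they do not make the full sample available at 1 week.

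A reader might also infer that Aim 1 will be biased by selection. The article does not establish this either. It specifies no complete-case analysis, and the Statistical plan foresees sensitivity analyses for missing data and possible multiple imputation. If having a 1-week stool depended only on prenatal stress, which is in the model, the regression of microbiome on stress would not be biased by it; the cost would be precision and exposure range. Bias needs a further link to the microbiome. Imputation, for its part, does not create the outcomes that the power statement counts.

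Finally, reading baseline as each dyad's first visit would restore the 300, but it conflicts with the 1-week definition in the aims.

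**Conclusion.** The stated N for Aim 1 is contradicted by the enrolment rule, nothing in the article reconciles the two, and Aim 1 carries no allowance. That much rests on the text alone. The numerical consequence is conditional. With figures simulated at N = 300, two-sided 5% and an assumed 10% to 30% without a 1-week stool, power falls to between 90% and 82% for r = 0.22, and between 74% and 63% for r = 0.18. With a smaller effective N, the power may hold but its described basis does not. Either way the sentence needs correcting. This is an internal inconsistency that should be resolved, not a demonstrated arithmetic error. Selection related to stress is a possibility to guard against, not a finding.

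**What to change.** Replace the full-sample statement with the expected number of usable 1-week stools. This can be counted now: the article reports 175 enrolled dyads in Study design and 185 participants in Participant recruitment. Restate Aim 1 power at that number, and give the alpha, the number of stress indicators and the loadings used in the simulation.

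As a low-cost addition, fit the Aim 1 structural equation model by full-information likelihood, or weight by the inverse probability of having a 1-week stool, using prenatal data already held. Restrict this to parent-study women eligible for the infant cohort, since the whole parent cohort may include women the infant study excludes. Women without a stool inform only the stress measurement model, so this step guards against selection but does little to restore power.

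The cost is a count, a rerun of the simulation and one analysis step. No new data are needed.
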